## Abstract

**Introduction:**

Traumatic brain injury (TBI) is a common presentation in the prehospital environment. At present, paramedics do not routinely use tools to identify low-risk patients who could be left at scene or taken to a local hospital rather than a major trauma centre. The Canadian CT Head Rule (CCHR) was developed to guide the use of CT imaging in hospital. It has not been evaluated in the prehospital setting. We aim to address this gap by evaluating the feasibility and acceptability of implementing the CCHR to patients and paramedics, and the feasibility of conducting a full-scale clinical trial of its use.

**Methods and analysis:**

We will recruit adult patients who are being transported to an emergency department (ED) by ambulance after suffering a mild TBI. Paramedics will prospectively collect data for the CCHR. All patients will be transported to the ED, where deferred consent will be taken and the treating clinician will reassess the CCHR, blinded to paramedic interpretation. The primary clinical outcome will be neurosurgically significant TBI. Feasibility outcomes include recruitment and attrition rates. We will assess acceptability of the CCHR to paramedics using the Ottawa Acceptability of Decision Rules Instrument. Interobserver reliability of the CCHR will be assessed between paramedics and the treating clinician in the ED. Participating paramedics and patients will be invited to participate in semistructured interviews to explore the acceptability of trial processes and facilitators and barriers to the use of the CCHR in practice. Data will be analysed thematically. We anticipate recruiting approximately 100 patients over 6 months.

**Ethics and dissemination:**

This study was approved by the Health Research Authority and the Research Ethics Committee (REC reference: 22/NW/0358). The results will be published in a peer-reviewed journal, presented at conferences and will be incorporated into a doctoral thesis.

**Trial registration number:**

ISRCTN92566288.

Strengths and limitations of this studyTo our knowledge, this study will be the first to evaluate the feasibility and acceptability of implementing the Canadian CT Head Rule (CCHR) in the prehospital setting, filling an important gap in the existing literature.The study has a limited sample size, as its primary objective is to assess the acceptability and feasibility of implementing the CCHR in the prehospital setting.The findings of this study will be used in the future to inform the design of a fully powered diagnostic test accuracy study.

## Introduction

Traumatic brain injury (TBI) is widely recognised as being one of the most common causes of death and disability especially among young adults^1^; however, it is becoming more frequent in the older population.^2^ TBI is a heterogeneous pathophysiological condition that varies widely in terms of its aetiology, severity, clinical presentation and outcomes. This broad spectrum of severity creates clinical challenges, such as the inappropriate allocation of major trauma centre (MTC) resources to less serious cases.^3^

The goal of prehospital trauma triage tools is to efficiently and promptly direct patients to the medical facility best suited to their needs and the available resources. Most TBIs are mild in nature and can be treated at a local trauma unit or non-trauma centres.^4^ There is no evidence indicating that these patients should be transported to a specialist neurological centre. Therefore, accurate prehospital triage of these patients will reduce the likelihood of MTCs being overwhelmed with patients suffering from mild TBI or non-TBI injuries as well as reducing the costs that might result from overtriaging patients who are unlikely to benefit from the costly resources of an MTC.

The cranial CT scan is considered the gold standard for the emergency evaluation of patients with suspected intracranial injury.^5^ Various validated clinical decision tools, including the Canadian CT Head Rule (CCHR), have been developed through extensive prospective studies to assess the need for a CT scan after a minor head injury.^6 7^ Comparative studies have examined various clinical tools, most notably the New Orleans Criteria and the CCHR, revealing that although both demonstrate similar sensitivity, the CCHR generally provides greater specificity.^8–10^ Several studies have shown that the CCHR achieves 100% sensitivity in identifying neurosurgical needs and captures significant CT findings, offering greater specificity (36–65%) compared with other decision rules.^9–11^

The National Institute for Health and Care Excellence (NICE) has guidelines that largely follow the CCHR to determine when to perform CT scans in cases of head injury.^12^ This approach is supported by evidence showing that the CCHR rule is the most cost-effective among various decision rules evaluated.^13^ Although the number of CT scans has increased, the admission rate has been halved (from 9% to 4%), resulting in a saving of £3381 per 100 patients.^14 15^ The implementation of NICE head injury guidelines indicates that the higher costs of CT scans, averaging about £100 per scan, are balanced by the savings from reduced hospital admissions, estimated to be around £847 per patient.^13^

Considering that paramedics have access to all the necessary data for the CCHR, it might be feasible to use the CCHR in the prehospital setting to promote consistency in care and optimise resource utilisation. Prehospital implementation of the CCHR could enable paramedics to transport patients to lower-level or non-trauma centres, or even (if shown to be sufficiently sensitive) safely leave patients at the scene. However, no studies have explored whether clinical decision aids can be used to rule out neurosurgically significant TBI in patients with apparently mild TBI in the prehospital field.

In England and Wales, around 1 million emergency department (ED) visits annually are for head injuries, with 90% being minor (Glasgow Coma Scale (GCS) 13–15), and the majority of patients are transported by ambulance services.^16^ Optimising healthcare resource use and enhancing patient care experiences can be greatly advanced by reducing unnecessary ambulance transports to distant MTCs, when appropriate and feasible.^17 18^ Integrating the CCHR into prehospital field presents a valuable opportunity to improve the triage process, allowing prehospital care providers to make informed decisions regarding the necessity of hospital transport and the level of care required, thereby optimising healthcare resources and potentially reducing healthcare costs. This approach also opens the door to exploring alternative care pathways for such patients, ensuring they receive appropriate and timely care without overwhelming hospital resources.

To obtain reliable estimates of the diagnostic accuracy of the CCHR, a large, multicentre study is warranted. This would be expensive and time-consuming; however, the findings of such a study could inform changes to clinical practice. Successful delivery of such research would depend heavily on adherence to the study protocol and the rates of recruitment attrition. Before embarking on such a study, it is necessary to evaluate the viability of the intended study processes.^19^

The purpose of this study is to establish the feasibility of a fully powered diagnostic test accuracy study to evaluate the accuracy of the CCHR when applied by paramedics to patients with mild TBI in the prehospital setting.

### Research question

Is it feasible to conduct a prospective clinical study to evaluate the diagnostic accuracy of the CCHR in the prehospital field to assist with making informed decisions regarding the appropriate level of care for patients with minor head injuries?

### Objectives

To determine the feasibility of a study to evaluate the diagnostic accuracy of the CCHR in the prehospital environment.To evaluate the interobserver reliability of the CCHR between prehospital clinicians and ED physicians.To evaluate the clinical sensibility of using the CCHR in the prehospital environment and to measure paramedics’ attitudes toward the CCHR.To obtain an estimate of the diagnostic accuracy of the CCHR when used in the prehospital setting.

## Methods

### Study design and setting

A prospective, multicentre feasibility study will be conducted in Greater Manchester, a region within the service area of the North West Ambulance Service (NWAS). NWAS is a National Health Service (NHS) trust that provides emergency medical services and patient transportation across the North West region of England. It covers an extensive area of over 5400 square miles, providing emergency and non-emergency medical services to a population of over 7.5 million people. There are two adult MTCs in Greater Manchester, which are part of the network covered by NWAS. These are Salford Royal Hospital and Manchester Royal Infirmary. In addition to these MTCs, the network also includes several trauma units and local emergency hospitals, each playing a distinct role in the trauma care pathway. The study protocol has been prospectively registered through the ISRCTN registry (study ID: ISRCTN92566288).

For the purpose of the study, we modified the CCHR for prehospital use (table 1). The original rule excluded patients <16 years, patients with a bleeding disorder or users of oral anticoagulants and/or antiplatelet and or those experiencing a post-traumatic seizure. In the modified version, only patients under the age of 16 years will be excluded. However, patients taking anticoagulant or antiplatelet drugs will be included and will be considered ‘positive’ with the modified CCHR (ie, would require transport to hospital). Anticoagulant use is defined as the use of warfarin, edoxaban, dabigatran, apixaban and rivaroxaban. Antiplatelets use is defined as the use of clopidogrel, ticlopidine, ticagrelor, dipyridamole and prasugrel. Figure 1 displays a visual representation of the recruitment process. At the time of writing in April 2024, the study is actively in the recruitment phase and open for participant enrolment.

**Table 1 T1:** The original and modified versions of the Canadian CT Head Rule

Canadian CT Head Rule (original)	Canadian CT Head Rule (modified)
**High risk (for neurosurgical interventions)**	**High risk (for neurosurgical interventions)**
GCS score <15 at 2 hours after injury	GCS score <15 at presentation
Suspected open or depressed skull fracture	Suspected open or depressed skull fracture
Any sign of basal skull fracture	Any sign of basal skull fracture
Vomiting ≥2 episodes	Vomiting ≥2 episodes
Age ≥65 years	Age ≥65 years
**Medium risk (for brain injury on CT)**	**Medium risk (for brain injury on CT)**
Amnesia before impact >30 min	Amnesia before impact >30 min
Dangerous mechanism of injury (pedestrian struck by vehicle, ejection from vehicle, fall from >3 ft or >5 stairs	Dangerous mechanism of injury (pedestrian struck by vehicle, ejection from vehicle, fall from >3 ft or >5 stairs

Patients with any positive high-risk or medium-risk criteria will be considered to have a ‘positive’ outcome (requiring transport to a hospital).

GCS, Glasgow Coma Scale.

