### Outcomes

We will study the following feasibility outcomes:

The number of eligible patients who are approached.The proportion of those approached who consent to participate in the study.The completeness of data collection.The completeness of follow-up.The number and proportion of patients with neurosurgically significant TBI.Determination of the interobserver reliability of the CCHR completed by prehospital care providers and ED physicians.Determination of the interobserver reliability for each component of the CCHR assessed by prehospital care providers and ED physicians.The diagnostic performance and clinical sensibility of the CCHR in the opinion of attending paramedics.Determination of the acceptability of trial processes as perceived by paramedics and patients.

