#### In-hospital environment

REDCap will be used to collect hospital data, and a paper CRF will also be available as an alternative. Emergency physicians at the receiving hospital will assess the patients to determine whether a CT scan is necessary in accordance with local and national guidelines. Relevant data about imaging studies undertaken and their findings will be extracted from hospital records. The routine radiology reports will be used to extract the follow-up data required for this study. Where there is uncertainty about the interpretation of the radiology report, a second radiologist will be asked to interpret the images.

Further, emergency physicians at the receiving hospitals will be asked to assess the patients using the CCHR and record their findings, blinded to the assessments made by participating paramedics. These data will be used to determine the interobserver reliability of the CCHR between paramedics in the prehospital environment and clinicians in the ED. Additionally, in-hospital medical records will be reviewed to obtain information regarding neurosurgical interventions undertaken during the patient’s hospital admission.

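### The text makes anticoagulant or antiplatelet use rule-positive, but the modified CCHR in Table 1 has no such criterion, and the analyses name only 'the CCHR'

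*Protocol article*

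**What the plan says.** All places are in the protocol article.

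- **Study design and setting, text.** The authors state that "we modified the CCHR for prehospital use (table 1"), so Table 1 is offered as the definition. The original rule is said to exclude, besides children, "patients with a bleeding disorder or users of oral anticoagulants and/or antiplatelet and or those experiencing a post-traumatic seizure". Then: "In the modified version, only patients under the age of 16 years will be excluded". Drug users are dealt with explicitly: "patients taking anticoagulant or antiplatelet drugs will be included and will be considered" positive. The text lists the drugs that count in each class.
- **Table 1.** The modified column has five high-risk and two medium-risk criteria. None is anticoagulant or antiplatelet use. It differs from the original column only in the GCS row, whose two cells read "GCS score <15 at 2 hours after injury GCS score <15 at presentation". The footnote says: "Patients with any positive high-risk or medium-risk criteria will be considered to have a" positive outcome.
- **In-hospital environment.** For the second rating, "emergency physicians at the receiving hospitals will be asked to assess the patients using the CCHR and record their findings", blinded to the paramedic's assessment. The version is not named.
- **Outcomes and Quantitative data.** The outcomes include "Determination of the interobserver reliability for each component of the CCHR". The analysis section plans Cohen's kappa, sensitivity, specificity and likelihood ratios, again for 'the CCHR' with no version.
- **Prehospital setting (Data collection).** Anticoagulant use is a named data item. Antiplatelet use is not, although the list is stated to be non-exhaustive.

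**The concern.** An index test has to be one fixed algorithm. Here the table cited as the rule leaves out something the text treats as sufficient for a positive result. Someone who builds a CRF or an analysis script from Table 1 gets a different test from someone who works from the paragraph above it.

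Two stated objectives rest on that test: interobserver reliability and a first estimate of accuracy. Accuracy moves with whichever definition is programmed. Kappa is affected in a different way. If both raters' results come from the same list, right or wrong, the definition adds no disagreement. If the drug item counts for one rater only, kappa absorbs a difference between forms and reports it as disagreement between observers. The component analysis also depends on the answer, because the number of components does.

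**Working it through.** **Side-by-side reading.** Take a patient aged 40 on apixaban, GCS 15, meeting none of the seven listed criteria. By the text the result is positive. By Table 1 and its footnote no listed criterion is met, so a derivation built from the table returns negative. Age 65 or over is already a criterion, so the affected group is listed-drug users under 65 with no other positive feature.

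**Size.** The article gives no drug prevalence, no expected rule positivity and no target kappa, so there is no stated figure to reproduce. The only plan figure used is the anticipated sample of about 100. The rest is assumed:

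- p, the share positive on the seven listed criteria: 50–80%;
- q, the share of the remaining patients who take a listed drug: 5–20%;
- 8 traumatic lesions per 100, all in patients positive on the listed criteria;
- the two raters agree perfectly on every bedside finding.

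Patients who change class per 100: b = 100(1 − p)q.

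Specificity is 100(1 − p)/92 by the table and 100(1 − p)(1 − q)/92 by the text, a difference of b/92.

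Kappa if only one rater's form carries the drug item: the 2×2 cells are a = 100p (both positive), b discordant one way, 0 the other way, and d = 100(1 − p)(1 − q) (both negative). With po = (a + d)/100 and pe = [(a + b)a + d(b + d)]/100², kappa = (po − pe)/(1 − pe).

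Worked case, p = 0.5 and q = 0.20: a = 50, b = 10, d = 40. po = 0.90. pe = (60 × 50 + 40 × 50)/10,000 = 0.50. Kappa = 0.40/0.50 = 0.80. Specificity is 50/92 = 0.543 by the table and 40/92 = 0.435 by the text.

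| p | q | b per 100 | kappa | specificity, table → text |
|---|---|---|---|---|
| 0.5 | 0.05 | 2.5 | 0.95 | 0.543 → 0.516 |
| 0.5 | 0.20 | 10 | 0.80 | 0.543 → 0.435 |
| 0.6 | 0.05 | 2 | 0.96 | 0.435 → 0.413 |
| 0.6 | 0.20 | 8 | 0.83 | 0.435 → 0.348 |
| 0.7 | 0.05 | 1.5 | 0.96 | 0.326 → 0.310 |
| 0.7 | 0.20 | 6 | 0.85 | 0.326 → 0.261 |
| 0.8 | 0.05 | 1 | 0.97 | 0.217 → 0.207 |
| 0.8 | 0.20 | 4 | 0.87 | 0.217 → 0.174 |

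Over this grid kappa falls from 1.00 by 0.03 to 0.20, and specificity shifts by 1/92 = 1.1 to 10/92 = 10.9 points. The two effects need different conditions. The specificity shift arises whenever table and text give different derivations; the kappa loss arises only if the raters' forms or derivations differ.

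Sensitivity is unchanged under the assumption that all lesions are in listed-criteria positives. If one of D lesion patients is positive only through the drug item, sensitivity moves by 1/D: 20 points for D = 5, 10 points for D = 10.

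With a single rule applied to both raters, disagreement due to definition is zero by construction.

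**The case against.** **The text already fixes the rule.** The Table 1 footnote says that any listed criterion makes a patient positive; it does not say that nothing else does. Text and table can be read as additive, with the table merely incomplete. This is a fair reading and probably the intended one. A reader might go further and conclude that the plan requires the same patient to be both positive and negative; the wording does not support that. What stands is that the table presented as the modified rule omits one of its sufficient conditions.

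**The ED version can be inferred.** A reader might infer that ED physicians will apply the original rule. The article points the other way: the rule was modified for this study, the abstract has the treating clinician reassess the CCHR, and the original rule excludes patients whom this study enrols. An unseen CRF may settle it, and nothing shows that the two raters' forms differ. The kappa loss is therefore a conditional risk, not a demonstrated error.

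**Seizure and bleeding disorder.** One might say that these patients have no classification at all. By default they are judged on the listed criteria, since only drug users are singled out. An explicit sentence would remove doubt, but this is not a contradiction.

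**GCS timing.** Paramedic and physician see the patient at different times, so a change from GCS 14 to 15 can create discordance without observer error. That is inherent in comparing prehospital with ED raters, and no rewording removes it. Prehospital GCS and GCS on hospital arrival are both recorded, so its effect can be examined.

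**Low stakes.** The analyses are declared exploratory and descriptive, and no row of Table 2 uses kappa or accuracy. Both are true and they limit the weight of the point. They do not make an estimate from an ambiguous index test easier to interpret when it is used to design the definitive study.

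**Conclusion.** The modified CCHR is defined inconsistently between the text and the table cited as its definition, and later sections do not say which version they mean. This is worth correcting before analysis, but it does not threaten the go/stop decision.

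The size cannot be derived from the article. Under the assumed 50–80% positivity on listed criteria and 5–20% listed-drug use among the rest, 1–10 patients per 100 change rule result. Specificity then shifts by about 1–11 points (8 lesions per 100, all positive on listed criteria). Kappa falls by about 0.03–0.20, and only if the drug item reaches one rater's form and not the other's.

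A reader might take a loss above 0.10 as the expected effect. At 65% positivity on the listed criteria, 5 discordant patients per 100 do cost about 0.11: po = 0.95, pe = (70 × 65 + 30 × 35)/10,000 = 0.56, kappa = 0.39/0.44 = 0.89. But both inputs are assumptions, and the low end is just as compatible with the article.

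**What to change.** 1. Reconcile Table 1 with the text into one list of criteria that defines the modified rule. State in it how patients with a bleeding disorder or a post-traumatic seizure are classified. This review takes no view on which classification is right.
2. Under In-hospital environment and Quantitative data, state that both raters and all analyses use this modified rule, and give the time point of the GCS item for each rater.
3. Derive positive or negative from the recorded items by one algorithm for both raters.
4. If the reconciled list carries the drug item, include it in the component reliability analysis.
5. As an exploratory addition, report kappa with and without the GCS item.

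The cost is mainly wording, one derivation and one extra tabulation. The caveat is data capture. Confirm that antiplatelet use is on both CRFs, since the prehospital list names only anticoagulant use. Recruitment was open in April 2024, so any change to a form would create two data versions and must be dated and reported.

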**Figure 1 F1:**
[figure not shown]
Study flow chart. CCHR, Canadian CT Head Rule.

### Participants

#### Patient eligibility

##### Inclusion criteria

This study will be conducted using a convenience sample of adult patients with mild TBI who will be transported to Northern Care Alliance NHS Foundation Trust and Manchester University Hospital NHS Foundation Trust. Only those patients who meet the following criteria will be included:

Adult patients (≥16 years) who receive an emergency ambulance response for a primary complaint of head injury. This includes those involved in motor vehicle crashes (MVCs), provided they meet the other inclusion criteria.GCS score of 13–15 at the time of assessment by attending paramedics.Patients transported to the hospital for clinical care.

##### Exclusion criteria

Secondary transfers of patients including interfacility transport.Penetrating skull injury.Trauma to other body regions that require clinical treatment, indicating multisystem trauma. This includes patients involved in MVCs where the treating paramedic assesses the presence of injuries beyond isolated head trauma that require clinical intervention. Paramedics will apply their clinical judgement to identify and exclude such cases.Prisoners.

### Study duration and sample size

This is a feasibility study, in which evaluating recruitment rate is an outcome; therefore, it is not possible to specify a sample size a priori. However, we intend to recruit participants for a fixed period of 6 months. Based on data routinely collected by the Manchester University NHS Foundation Trust, a total of 5332 patients arrived in the ED by ambulance with a primary complaint of head injury over a period of 4 years and 9 months up to November 2020. We intend to recruit participants from two similarly sized MTCs. We anticipate that approximately 1100 patients will be eligible to participate in this study during the recruitment period. Accounting for the availability of trained paramedics on the study delegation log and concurrent injuries to other body systems that would exclude patients from participating in this study, approximately 100 participants can be recruited to this study. This number of participants is generally accepted as being appropriate for studies that focus on assessing feasibility and acceptability.^20^

